#### Recruitment, randomisation and retention

The right of the patient to refuse to participate in the trial without giving reasons must be respected. Those recruiting and randomising participants will rigorously maintain a position of equipoise and employ explanations that are consistent with this [55]. All the participating clinicians regard all the four treatments as potentially effective and are of the view that most patients seen will accept randomisation if it is fully and openly explained. Some patients are initially sceptical about treatment effectiveness but are willing to accept any of these recommended treatments as long the treatment is appropriately explained and delivered. Therefore, we do not anticipate a difficulty either in acceptability of the proposed treatments, with recruitment into the trial, or acceptance of randomisation. We emphasise that we make this statement based on our having completed six trials of treatment for CFS/ME. After the patient has entered the trial, the clinic doctor must remain free to give alternative treatment to that specified in the protocol, at any stage, if he/she feels it to be in the best interest of the patient.

#### Compliance

The trial will be conducted in compliance with the Declaration of Helsinki, the trial protocol, MRC Good Clinical Practice (GCP) guidance, the Data Protection Act (1998), the Multi-centre Research Ethics Committee (MREC) and Local Research Ethics Committees (LREC) approvals and other regulatory requirements, as appropriate. The final trial publication will include all items recommended under CONSORT.

#### Sponsor

The main sponsor is Barts and the London, Queen Mary School of Medicine and Dentistry.

#### Research Ethics Approval (MREC)

Ethical approval for the PACE trial was given by the West Midlands MREC (reference number MREC/02/7/89). Local REC approvals have been sought and obtained as required.

#### Indemnity

Each centre taking part in the trial will seek local approval and indemnity through their NHS R&D department. As an automatic consequence of this, local NHS indemnity will apply to the PACE trial. Details of local indemnity arrangements can be obtained through each centre's NHS R&D department.

### Analyses

#### Assumptions

The existing evidence does not allow precise estimates of improvement with the trial treatments. However the available data suggests that at one year follow up, 50 to 63% of participants with CFS/ME had a positive outcome, by intention to treat, in the three RCTs of rehabilitative CBT [18,25,26], with 69% improved after an educational rehabilitation that closely resembled CBT [43]. This compares to 18 and 63% improved in the two RCTs of GET [23,24], and 47% improvement in a clinical audit of GET [56]. Having usual rather than specialist medical care allowed 6% to 17% to improve by one year in two RCTs [18,25]. There are no previous RCTs of APT to guide us [11,12], but we estimate that APT will be at least as effective as the control treatments of relaxation and flexibility used in previous RCTs, with 26% to 27% improved on primary outcomes [23,26]. We propose that a clinically important difference would be between 2 and 3 times the improvement rate of SSMC.

#### Power analyses

Our planned intention to treat analyses will compare APT against SSMC alone, and both CBT and GET against APT. Assuming α = 5% and a power of 90%, we require a minimum of 135 participants in the SSMC alone and APT groups, 80 participants in the GET group and 40 in the CBT group [57]. However these last two numbers are insufficient to study predictors, process, or cost-effectiveness. We will not be able to get a precise estimate of the difference between CBT and GET, though our estimates will be useful in planning future trials. As an example, to detect a difference in response rates of 50% and 60%, with 90% power, would require 520 participants per group; numbers beyond a realistic two-arm trial. Therefore, we will study equal numbers of 135 participants in each of the four arms, which gives us greater than 90% power to study differences in efficacy between APT and both CBT and GET. We will adjust our numbers for dropouts, at the same time as designing the trial and its management to minimise dropouts. Dropout rates were 12 and 33% in the two studies of GET [23,24] and 3, 10, and 40% in the three studies of rehabilitative CBT [18,25,26]. On the basis of our own previous trials, we estimate a dropout rate of 10%. We therefore require approximately 150 participants in each treatment group, or 600 participants in all. Calculation of the sample size required to detect economic differences between treatment groups requires data of cost per change in outcome, which is not currently available.

#### Analysis plan

A full Analysis Strategy will be developed, independently of looking at the trial database, and before undertaking any analysis. This paper summarises the analysis plan.

#### Secondary analyses of efficacy

The secondary continuous outcomes will be analysed by repeated measures analysis of variance using a linear mixed model with AR(1) covariance structure, and including centre, depressive disorder, CDC and London criteria and baseline values as covariates. The same contrasts as those specified for the primary outcomes will be extracted. A summary measure, the area under the curve, will also be reported.

A secondary, per protocol, analysis restricted to participants who complete a minimum of 12 weeks of treatment (representing the mid point in therapy time), will also be performed.

Further secondary sensitivity analyses will be used to assess the robustness of conclusions for missing primary outcomes; these will employ repeated binary outcomes, multiple imputation, and imputation analysing all possible outcomes [58].

Loss to follow-up, departures from randomised treatment protocols, and the prevalence of serious adverse events, will be reported at 13, 26, 39, and 52 weeks from randomisation.

Results from all analyses will be summarised as differences between percentages or means together with 95% confidence limits (CL). The significance level for all analyses of primary outcome variables will be P = 0.05 (two-sided); for secondary outcome variables, P = 0.01 (two-sided) unless profiles of response can be specified in advance.

Prior to writing the Analysis Strategy a consensus will be reached on the profiles of response for each secondary outcome within each of the four treatment groups.

#### Predictions and process of treatment

Associations between post-treatment outcomes and both predictor and process variables (including demographic, illness duration, and other putative clinical indicators) will be examined using multiple linear and logistic regression modelling techniques, including a limited examination of interactions both amongst pairs of predictors and between predictors and treatment groups. We anticipate that the sample size will be sufficient to identify important general predictors from a random-split, training set of two thirds (~400), with partial validation in the remainder, used as a test set. Shrinkage techniques (to allow for over-optimism in variable selection) will be applied in the development of a prognostic model to be applied to participants outside the trial.

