#### Secondary objectives

The secondary analyses are exploratory but we will be guided by previously published findings.

(1) Do different treatments have differential effects on outcomes (i.e. fatigue versus physical disability)?

(2) What baseline factors (other than randomised treatment) predict a reduction in (i) fatigue, (ii) disability in all participants?

(3) Are there differential predictors of response to APT, CBT, GET, and SSMC (i.e. treatment-covariate interactions)?

(4) Are there changes in factors (time-dependent covariates) during the earlier stages of treatment that (after controlling for baseline overall and differential predictors) are associated with outcome 1 year after randomisation?

(5) Are the differences across treatment groups in the primary outcomes associated with similar differences in secondary outcomes (e.g. in global change, mood, quality of life and objective measures of physical activity)?

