### Telephone assessment

The RN will contact patients within 24 hours of receipt of referral, who have been referred by the clinic doctor for the PACE trial, by telephone. The RN will check that the patient has received a Participant Information Sheet from the clinic doctor, and if they express interest in the trial, will arrange a date for the patient to attend the first research assessment interview (visit 1) as soon as possible (within one week of referral, but not more quickly than 48 hours after receipt of the Participant Information Sheet).

### Eligibility assessment and consent for assessment – visit 1

All of the following eligibility criteria must be fulfilled for the patient to participate:

1. The patient has a clinical diagnosis of CFS [2].

2. The patient does not have treatment needs that would make participation in the PACE trial inappropriate.

3. The patient is aged 18 years or above.

4. The patient can speak and read English at a level adequate for participation in the trial, as assessed by the RN. The reasons for this include the need to self-rate written primary and secondary outcomes using scales that have not been validated in non-English languages; the need to receive therapy that can be checked for quality and manual adherence; and the prohibitive cost of providing therapy in more than one language.

5. The Chalder Fatigue Questionnaire score is 6 or more [27].

6. The SF-36 physical function sub-scale score is 65 or less [28].

7. The Structured Clinical Interview for DSM-IV (SCID i/P; non-patient edition with psychotic screen) [30], will be used to exclude patients with psychiatric exclusions [2]. If a participant or patient is found to have a current psychiatric diagnosis on the SCID, the RN will inform the clinic doctor. All SCIDs will be audio-recorded for the purposes of quality control and RN supervision; the supervision being provided by the centre leader or their nominated deputy.

8. Patients who are considered by the RN in discussion with their centre leader to be unable to do one or more of the trial therapies or to complete all trial measures (travel expenses will be offered for therapy and research assessments).

9. There is no contra-indication to any of the treatments that might be provided in the trial.

10. Permission has been obtained to review medical notes.

In addition, the following assessments will be completed at baseline visit 1:

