#### Predictors

1. Sex

2. Age

3. Duration of CFS/ME (months)

4. 1 week of actigraphy [18] (as initiated at visit 1 with the research nurse)

5. Body mass index (measure weight in kg and height in metres)

6. The CDC criteria for CFS [1]

7. The London criteria for myalgic encephalomyelitis [40]

8. Presence or absence of "fibromyalgia" [41]

9. Jenkins sleep scale of subjective sleep problems [37]

10. Symptom interpretation questionnaire [34]

11. Preferred treatment group

12. Self-efficacy for managing chronic disease scale [32]

13. Somatisation (from 15 item physical symptoms PHQ sub-scale) [35]

14. Depressive disorder (major and minor depressive disorder, dysthymia by DSMIV) (from SCID) [30]

15. The Hospital Anxiety and Depression Scale (HADS) [38] combined score

16. Receipt of ill-health benefits or pension

17. In dispute/negotiation of benefits or pension

18. Current and specific membership of a self-help group (specific question)

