#### Process variables

1. Step test of fitness [43]

2. Borg Scale of perceived physical exertion [44]

3. The symptom interpretation questionnaire [34]

4. Exercise and activity scale

5. PHQ symptom sub-scale

6. HADS scale combined score

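### The predictor and process lists leave out baseline fatigue and physical function, and no adjustment for them is stated, so markers of baseline severity may appear as independent predictors

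*Protocol article*

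**What the plan says.** Secondary objective 2 asks: "What baseline factors (other than randomised treatment) predict a reduction in (i) fatigue, (ii) disability in all participants". Objective 3 asks about differential predictors by treatment. Objective 4 asks whether early changes are associated with the one-year outcome once baseline predictors have been controlled for.

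The section Predictions and process of treatment describes the models: "Associations between post-treatment outcomes and both predictor and process variables (including demographic, illness duration, and other putative clinical indicators) will be examined" by multiple linear and logistic regression, "including a limited examination of interactions both amongst pairs of predictors and between predictors and treatment groups". A random two thirds of the sample (about 400) is the training set and the rest is a test set. Shrinkage is applied to a prognostic model meant for people outside the trial.

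The Predictors section numbers 18 variables. Several are likely to track severity, for example "Somatisation (from 15 item physical symptoms PHQ sub-scale"), "15. The Hospital Anxiety and Depression Scale (HADS) [38] combined score" and "1 week of actigraphy [18] (as initiated at visit 1 with the research nurse"). Process variables lists six, among them "HADS scale combined score". Neither list contains the Chalder Fatigue Questionnaire or the SF-36 physical function sub-scale.

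Every participant has both scores at entry. The visit 1 eligibility criteria require a Chalder score of at least 6 and state: "The SF-36 physical function sub-scale score is 65 or less". For the mixed models of the secondary continuous outcomes, Secondary analyses of efficacy does name baseline values as covariates.

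**The concern.** A follow-up score depends on its own baseline. The two binary responses depend on it by construction, because each is a 50% change from baseline or a fixed threshold. If the baseline score is not in the model, any listed variable correlated with it can pick up part of that dependence and look like a predictor in its own right.

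Objective 2 concerns reduction in fatigue or disability, and a follow-up value modelled without its baseline does not answer that question. The same gap can reach the process models of objective 4, to the extent that the baseline predictors controlled for there come from the stated list.

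The planned safeguards do not catch this. Validation in the held-out third and shrinkage guard against over-optimism from variable selection. An association inherited from an omitted baseline score is a real marginal association, so it tends to replicate in the test set.

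**Working it through.** **1. The plan's own figure.** 600 × 2/3 = 400, the stated training set size. It reproduces.

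**2. Dependence of response on baseline** (rules under Primary outcome measures).

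Physical function: gain needed = min(75, 1.5 × baseline) − baseline.

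| Baseline SF-36 | Score needed | Gain needed |
|---|---|---|
| 10 | 15 | 5 |
| 20 | 30 | 10 |
| 50 | 75 | 25 |
| 65 | 75 | 10 |

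Fatigue (0–11): a baseline of 6 needs a drop of 3 (to 3). A baseline of 11 needs a score of 5.5 or less, so 5, a drop of 6.

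The hurdle varies with baseline, and for physical function it rises and then falls.

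**3. Size for one marker, by formula.** The documents give no correlations, so these are assumptions: marker–baseline correlation 0.2 to 0.4, baseline–outcome correlation 0.3 to 0.5, no effect of the marker given baseline.

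- Induced correlation = product of the two: 0.3 × 0.2 = 0.06 up to 0.5 × 0.4 = 0.20.
- Chance of p < 0.05 by Fisher z: Φ(z − 1.96) + Φ(−z − 1.96), with z = √(n − 3) × atanh(r).
- n = 400, r = 0.06: z = 19.92 × 0.0601 = 1.20, giving 22%.
- n = 400, r = 0.20: z = 19.92 × 0.2027 = 4.04, giving 98%.
- With the protocol's 10% dropout (n = 360): about 21% and 97%.

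**4. Size by simulation, n = 400, entry limited to SF-36 of 65 or less.** All inputs are assumed. Figures are the share of data sets in which a marker with no effect of its own has p < 0.05.

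- Set A: baseline about N(38, 16) truncated to 5–65, residual SD 22, slope of follow-up on baseline 0.5 or 0.8, marker–baseline correlation 0.2 to 0.4.
- Set B: baseline about N(40, 16) truncated to 5–65, mean gain 12, residual SD 18, slope 0.6 or 1.0, correlation 0.2 to 0.5.

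| Model | Result |
|---|---|
| Set A, one marker, no baseline, both outcome types | roughly 14–95% |
| Set A type, ten other similar markers in the model, no baseline | about 10–26% (a repeat gave 14–32% continuous, 9–20% binary) |
| Set B, one marker, no baseline, continuous score | 43–100% |
| Set B, one marker, no baseline, binary response | 8–94% |
| Baseline included | about 4–7% |

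The adjusted logistic model in set B carried baseline and its square, because of the non-monotone hurdle in step 2.

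**5. Direction.** In set B the mean marker coefficient without baseline was +1.69 to +6.96 for the continuous score and −0.06 to −0.36 (log odds) for the binary response. The same inert marker looks favourable on one scale and unfavourable on the other.

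The simulations cover physical function and main effects. Fatigue and the treatment interactions of objective 3 were not simulated.

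**The case against.** The strongest reply is that this is a summary article. The Analysis plan section defers to a full Analysis Strategy, the secondary analyses are called exploratory, and nothing says the baseline scores are barred. The covariate wording is open-ended, mentioning other clinical indicators. The Abstract promises that all analyses allow for stratification factors; centre is one of these and is not among the 18 predictors, so the list is evidently not the full covariate set. All of this stands, and it rules out saying that severity markers will be reported as predictors. It does not remove the point: the article does fix a detailed numbered list, two obvious entries are absent, and baseline adjustment is named for the mixed models but not here.

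The second reply is that the single-marker rates describe a bivariate test, whereas the plan is multiple regression with several variables that share the severity signal. This also stands. With ten similar markers the rate falls to about 10–26%, which is still above the nominal 5%.

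Three stronger readings are tempting and not supported:

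- A reader might infer that objective 4 adjusts only for the listed predictors. Its wording does not refer to the list or say so.
- A reader might infer that the models would simply show who was less ill at the start. For the binary physical function response the direction can reverse.
- A reader might infer that the prognostic model would be invalid. A severity marker can predict validly; omitting baseline may cost accuracy, but the error lies in reading the marker as an independent predictor.

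**Conclusion.** The point holds as a risk in exploratory models. The stated lists omit both baseline scores and the modelling section states no adjustment for them, although the scores are available for everyone and determine how hard it is to respond. Listed factors correlated with severity may then appear as independent predictors or process variables.

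The size rests entirely on assumed correlations, slopes and residual spread. The figure closest to the planned multivariable analysis is about 10–26% against a nominal 5%. The single-marker range of roughly 14–95% is an upper picture, and with weak correlation and a slope of 1.0 the binary response gave only 8%. Including baseline brings the rate to about 4–7%. The primary efficacy comparisons are not affected.

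**What to change.** Add the baseline Chalder fatigue score and the baseline SF-36 physical function score to the Predictors list. Under Predictions and process of treatment, state that every predictor and process model includes the baseline value of the outcome being modelled, with a non-linear term where the outcome is the binary response. State also that the models include treatment group and the stratification factors the Abstract already promises, and that these covariates are entered before other variables are selected.

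The cost is wording and a few degrees of freedom out of about 400: two for the two scores, plus one for each non-linear term. No new data are needed.

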**Methods/Design:**

600 patients, who meet operationalised diagnostic criteria for CFS, will be recruited from secondary care into a randomised trial of four treatments, stratified by current comorbid depressive episode and different CFS/ME criteria. The four treatments are standardised specialist medical care either given alone, or with adaptive pacing therapy or cognitive behaviour therapy or graded exercise therapy. Supplementary therapies will involve fourteen sessions over 23 weeks and a 'booster session' at 36 weeks. Outcome will be assessed at 12, 24, and 52 weeks after randomisation. Two primary outcomes of self-rated fatigue and physical function will assess differential effects of each treatment on these measures. Secondary outcomes include adverse events and reactions, subjective measures of symptoms, mood, sleep and function and objective measures of physical activity, fitness, cost-effectiveness and cost-utility. The primary analysis will be based on intention to treat and will use logistic regression models to compare treatments. Secondary outcomes will be analysed by repeated measures analysis of variance with a linear mixed model. All analyses will allow for stratification factors. Mediators and moderators will be explored using multiple linear and logistic regression techniques with interactive terms, with the sample split into two to allow validation of the initial models. Economic analyses will incorporate sensitivity measures.

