### Randomisation and Enrolment procedure

Participants will be allocated to one of the four trial arms (ratio 1:1:1:1) by the Mental Health & Neuroscience Clinical Trials Unit (MH&N CTU) based at the Institute of Psychiatry. Allocation will be stratified by *centre*, *CDC Criteria *(met or unmet), *London Criteria *(met or unmet) and *depressive disorder *(major, minor depressive episode and dysthymia being present or absent) using minimisation with a random component [45]. The stratification on these criteria is to ensure equal proportions in each treatment arm. The first N cases (N will not be disclosed) will be allocated using simple randomisation to further enhance allocation concealment.

Once an eligible participant has completed the baseline assessment and given written informed consent, the RN will contact the MH&N CTU for treatment allocation by facsimile, giving the criteria needed for randomisation. Minimisation is carried out with a random component using a customised Microsoft Access database which will be used to hold the basic details collected to facilitate subsequent verification and to generate the allocation. Allocation is concealed because an independent group are responsible for this allocation. The confirmation of stratification details and treatment allocation will be communicated by email or facsimile to the RN within 24 hours. The RN sends back an acknowledgement of receipt to the CTU. This whole procedure is kept independent and separate from the trial statisticians. The RN will on the same day inform the participant of his/her treatment group in person or by phone, and will also inform the SSMC doctor and appropriate therapist. The therapist will contact the participant to arrange the first treatment appointment as soon as possible (within 5 working days). The SSMC doctor will also arrange to see the participant within one month of treatment allocation. The individual assignments will be available to the local team on a need-to-know basis, with the exception of the trial statisticians.

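### The random two-thirds/one-third split is an inefficient internal validation of the predictor models; developing on all participants with resampling would use the data better

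*Protocol article*

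**What the plan says.** Under Predictions and process of treatment, the article plans linear and logistic regression of outcome on predictor and process variables. It allows a restricted look at interactions, both between pairs of predictors and between predictors and treatment. It expects the sample to be large enough to find the important general predictors from a "random-split, training set of two thirds (~400), with partial validation in the remainder, used as a test set". Shrinkage is planned for the prognostic model, which is meant for use outside the trial. The Abstract describes the same design more briefly, "with the sample split into two to allow validation of the initial models". No resampling method is mentioned, and no calculation supports the statement that the sample is large enough.

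The Predictors section lists 18 baseline candidates. The total comes from Power analyses: "We therefore require approximately 150 participants in each treatment group, or 600 participants in all". Secondary objectives describes these analyses as exploratory.

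**The concern.** The split is a stated method, given in two places, and not a detail left open. It withholds a third of the participants from the step that looks for predictors, then asks that third to judge the result. Both halves of the task suffer: selection and estimation rest on fewer people, and performance is estimated in a small test set. A different random split could select different predictors and report a different performance.

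At stake are secondary objectives 2 and 3 (general and differential predictors of response) and items (d) and (e) of the Rationale. Power analyses itself says that the minimum GET and CBT numbers for efficacy were too few for predictor work, which is part of why those arms were enlarged. It is then wasteful to keep a third of the sample out of that work.

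**Working it through.** **The plan's own figures.** 135 / (1 − 0.10) = 150 per arm; 150 × 4 = 600; 600 × 2/3 = 400 for training and 200 for testing. The stated ~400 is reproduced. With equal allocation, that is about 100 per arm for training and 50 for testing.

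**Precision of coefficients.** Standard errors scale with 1/√n, so the ratio is √(600/400) = √1.5 = 1.22.

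**Expected responders.** The Assumptions section gives ranges, not planning values, so the choices within them are assumptions. Usual care ("allowed 6% to 17% to improve by one year in two RCTs") stands in for SSMC.

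| | SSMC | APT | CBT | GET | Mean | Of 600 | Of 400 |
|---|---|---|---|---|---|---|---|
| Low | 6% | 26% | 50% | 18% | 25.0% | 150 | 100 |
| Middle | 11.5% | 26.5% | 56.5% | 47% | 35.4% | 212 | 142 |
| High | 17% | 27% | 63% | 63% | 42.5% | 255 | 170 |

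The middle GET value is the clinical audit figure.

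**Events per parameter, logistic models.** Parameters: 18 predictors + 3 treatment terms = 21.
- All 600: 212/21 = 10.1 (range 7.1 to 12.1).
- Training 400: 142/21 = 6.7 (range 4.8 to 8.1).
- Upper bound with every predictor-by-treatment term, 21 + 18 × 3 = 75 parameters: 2.8 against 1.9. The plan does not commit to fitting all of these.

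**Power to find a predictor.** Take a binary predictor split 50:50, overall response 35.4%, a 10-point difference (30.4% against 40.4%) and two-sided 5%. Power = Φ[(0.10 − 1.96 × SE₀)/SE₁], where SE₀ is the pooled and SE₁ the unpooled standard error.
- n = 600 (300 per level): SE₀ = 0.0391, SE₁ = 0.0388, power 73%.
- n = 400 (200 per level): SE₀ = 0.0478, SE₁ = 0.0476, power 55%.

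The smallest difference detectable with 80% power is 11.0 points at 600 and 13.4 points at 400.

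**Precision of the test set.** The Hanley–McNeil standard error at an assumed AUC of 0.70 and 35.4% response is 0.040 for 200 participants, a 95% half-width of ±0.08. For 600 it is 0.023, or ±0.045.

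**Simulation.** 150 simulated trials of 600 were run, with 18 independent predictors (six with real effects), treatment terms kept in, overall response about 35%, AIC-type backward elimination, and 60 bootstrap samples repeating the selection. The effect sizes are assumptions and no shrinkage was applied.

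| | Train 400 / test 200 | All 600 + bootstrap |
|---|---|---|
| True AUC of the model | 0.739 | 0.748 |
| Bias of the validated AUC | +0.001 | −0.003 |
| Root mean squared error of the validated AUC | 0.038 | 0.023 |
| Calibration slope of the model | 0.79 | 0.86 |

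**The case against.** The case for leaving the plan alone has real substance.

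- **The split is valid.** Its estimate was essentially unbiased in the simulation, and the AUC gain from changing is about 0.01. This stands. The point is about efficiency.
- **An untouched test set guards against choices made by judgement.** A bootstrap is sound only if every selection step can be repeated mechanically. This also stands, and it is the main downside of changing. Pre-specifying an automatable procedure meets it.
- **The analyses are exploratory, and a full Analysis Strategy is promised.** True, and this limits the weight of the point. Neither statement withdraws the split.
- **Events per parameter concerns only the logistic models.** Correct: a linear model with 400 participants and 21 terms has about 400/21 = 19 per term. The 1.22 ratio in standard errors applies to both kinds of model.
- **Shrinkage is planned.** It tempers over-optimism, so the calibration gap in the simulation may overstate the gap under the plan. It does not restore power to find predictors or steady the test-set estimate.

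A reader might infer more than the article supports:

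- *That ~400 overlooks the 10% drop-out.* Primary analyses of efficacy classes most participants not followed to one year as non-responders, so nearly all 600 have a binary response status. Only for continuous outcomes might the figure be nearer 540 × 2/3 = 360, and the loss would then affect either approach.
- *That a third of the data is thrown away.* It is used, for testing.
- *That the split is passed off as external validation.* The article claims only partial validation. A bootstrap is internal too.
- *That the models will run at about 2 events per term.* That assumes all 54 predictor-by-treatment terms, whereas the article plans a limited set. Using all 600 would raise that worst case only to 2.8.

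**Conclusion.** The point holds as one of efficiency. Compared with using all 600, the planned split enlarges development standard errors by a factor of 1.22. It lowers expected responders from about 212 to 142 and events per parameter for main effects from about 10 to 7. Power for a 10-point difference on a balanced predictor falls from about 73% to 55%. In the simulation, the error of the validated AUC was 0.038 against 0.023 with the bootstrap. Discrimination hardly changes.

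The factor of 1.22 follows from the stated sizes alone. The responder counts and power rest on assumed values within the cited response ranges, and the simulation on assumed effects without shrinkage. The consequence is confined to exploratory secondary objectives and does not touch the efficacy analyses. The change is worth making, but the trial does not depend on it.

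**What to change.** In Predictions and process of treatment, replace the split with the following:

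1. Develop each model on all participants with outcome data, and keep the planned shrinkage.
2. Pre-specify the candidate predictors, the limited set of interactions and the selection rule, in a form that can be run automatically.
3. Validate by bootstrap or repeated cross-validation, repeating every selection, interaction and shrinkage step in each resample.
4. Report optimism-corrected discrimination and calibration, described as internal validation.

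Amend the Abstract so that both places describe the same method.

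The change is not free. It needs more computing, and the analysts give up case-by-case judgement in choosing terms. It needs no change to recruitment, data collection or the efficacy analyses.
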